**CONFIDENTIAL**

\* Axillary temperature is usually used in China, tympanic temperature/temporal artery temperature = axillary temperature +0.5 °C. When persistent high fever occurs, the cause of high fever should be determined as soon as possible;

\*\* For constipation, attention should be paid to the changes before and after vaccination;

When judging severity, it can be judged as a next grade adverse event only when it meets the grading criteria of the previous one.

For clinical abnormalities not covered in the above table, the severity grading evaluation of adverse events should be carried out according to the following criteria.

| Grade 1                                                                                                     | Grade 2                                                                                                         | Grade 3                                                                                                             | Grade 4                                                                                                  | Grade 5 |
|-------------------------------------------------------------------------------------------------------------|-----------------------------------------------------------------------------------------------------------------|---------------------------------------------------------------------------------------------------------------------|----------------------------------------------------------------------------------------------------------|---------|
| Mild: Short-term (< 48h) or slight discomfort, which does not affect activities and does not need treatment | Moderate: Mild or moderate activity restriction, which may require medical treatment, no or only mild treatment | Severe: obvious activity
Restricted, need to see a doctor and receive treatment, and may need to be hospitalized | Critical: It may be life-threatening, severely limited in activities, and needs monitoring and treatment | Death   |

#### 4.5.3 Relationship between Adverse Events and Investigational Vaccines

**Impossible:** Adverse events occur due to other factors, and there is sufficient evidence to prove that adverse reactions/events are caused by other reasons and unrelated to d vaccination.

**Unlikely:** The occurrence of adverse events may be caused by other factors, such as the clinical status of the participant, other treatments or accompanying medication, which are inconsistent with the known adverse reactions of vaccination.

**Possible:** Adverse events are consistent with known investigational vaccine information, have a reasonable temporal sequence with vaccination, and/or have occurred for vaccination. There is also a causal relationship with the investigational vaccine, but it may also be related to other factors.

**Likely:** Adverse events are consistent with the known investigational vaccine information and have a causal relationship with the investigational vaccine, and cannot be explained by other factors, such as the clinical status of the participant, other treatments or concomitant medication.

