**CONFIDENTIAL**

**Definite:** Adverse events are consistent with the known investigational vaccine information and have a causal relationship with the investigational vaccine, and this relationship cannot be explained by other factors, such as the clinical status of the participant, other treatments or accompanying drugs. In addition, adverse events occurred repeatedly when the participants used the investigational vaccine again.

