### 7.7 Criteria for Suspension or Early Termination

- The number of participants with adverse reactions of severity Grade 3 or above exceeds 15% of the participants vaccinated in this subgroup;
- One case of Grade 4 adverse reaction related to vaccination or SUSAR;

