#### **10.3.4 Safety Evaluation**

Adverse events and serious adverse events will be coded using the Medical Dictionary for Regulatory Activities (MedDRA), and summarized by System Organ Class (SOC) and Preferred Term (PT). AEs will be summarized by solicited and unsolicited AEs as well. The Treatment Emergent Adverse Events (TEAEs) will be analyzed here. AEs occurring before vaccination will be listed.

All TEAEs, vaccine-related TEAEs, vaccine-unrelated TEAEs, Grade  $\geq 3$  TEAEs and vaccine-related Grade  $\geq 3$  TEAEs will be summarized by group. The frequency, participants and percentage in each group will be reported. Fisher exact test will be used to compare the difference between the groups. The strat time and severity of TEAEs will be summarized. The vaccine-related TEAEs and vaccine-unrelated TEAEs will be listed.

All TESAE, vaccine-related TESAEs and vaccine-unrelated TESAEs will be summarized by group. The frequency, participants and percentage in each group will be reported. Fisher exact test will be used to compare the difference between the groups. All TESAEs will be listed.

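### Section 4.5.3 builds expectedness into the causality scale, so a new reaction to NVSI-06-09 cannot be rated Likely or Definite and has no clear place elsewhere

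*Protocol*

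**What the plan says.** Section 4.5.3 of the protocol gives five causality categories: *Impossible*, *Unlikely*, *Possible*, *Likely* and *Definite*.

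- *Possible* begins: "Adverse events are consistent with known investigational vaccine information, have a reasonable temporal sequence with vaccination", with a further element joined by and/or. It then adds a causal relationship, with the remark that other factors may also play a part.
- *Likely* requires the event to be "consistent with the known investigational vaccine information and have a causal relationship with the investigational vaccine, and cannot be explained by other factors".
- *Definite* repeats those conditions and adds that "adverse events occurred repeatedly when the participants used the investigational vaccine again".
- *Unlikely* covers events that other factors may have caused, "which are inconsistent with the known adverse reactions of vaccination".

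Relatedness is then used in two places. Section 10.3.4 summarises "All TEAEs, vaccine-related TEAEs, vaccine-unrelated TEAEs", together with Grade 3 or higher events and the related subset of those, and compares groups by Fisher's exact test. Sections 5.1.4 and 7.7 tie suspension to Grade 3 or higher adverse reactions above 15%, and to "One case of Grade 4 adverse reaction related to vaccination or SUSAR".

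**The concern.** Whether a vaccine caused an event and whether the event was already known are separate questions. A SUSAR depends on keeping them apart, because it is a reaction that is suspected to be related and is also unexpected. Section 4.5.3 makes prior knowledge a condition of the two strongest grades and a marker for one of the two weak ones, so novelty counts against relatedness. In a trial of a new product, an unfamiliar reaction is what the safety assessment most needs to pick up.

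At stake are the related-event tables and tests in section 10.3.4 and the adverse-reaction limbs of the suspension criteria. Safety comparison is a primary objective (section 3.1). Section 4.5.3 is the only causality scale that the protocol states, and it names no reference document that would define what is known.

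**Working it through.** No arithmetic applies; the check is a reading of the sections against each other.

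**Step 1. Put a new reaction through the scale.** Take an event after NVSI-06-09 that is not among the known reactions, with and without a conceivable other cause.

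| Category | Role of prior knowledge | Role of other causes | New, other cause conceivable | New, no other cause |
|---|---|---|---|---|
| Impossible | none | other cause proven | no | no |
| Unlikely | inconsistent with known reactions | other factors may be the cause | fits | does not fit |
| Possible | consistency listed first, joined by and/or | other factors may contribute | only if and/or makes consistency optional | same, and the remark on other factors fits poorly |
| Likely | consistency required | other factors cannot explain it | closed | closed |
| Definite | consistency required | other factors cannot explain it; recurrence needed | closed | closed |

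The grammar of *Unlikely* is loose. The table reads the inconsistency as belonging to the event, which is the natural sense.

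**Step 2. Count.** Of the three categories on the related side, two (*Likely*, *Definite*) are closed to a new reaction and one (*Possible*) depends on how the and/or is read.

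**Step 3. Check whether Definite can be reached.** Each participant receives one booster (Synopsis, section 4.2, section 6.4). Section 5.1.2 excludes anyone who has had a COVID-19 vaccine other than the Vero Cell vaccine. Recurrence on repeat use of NVSI-06-09 therefore cannot be observed. Control participants have had two or three earlier Vero Cell doses, so recurrence is conceivable there if the control counts as an investigational vaccine, as the packaging text in section 6.2 suggests.

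**Step 4. Compare with the SUSAR text.** Sections 5.1.4 and 7.7 act on a SUSAR, and section 8.3 has the sponsor expedite reactions that are unexpected, serious and definitely or suspectedly related. For a new reaction, the scale leaves only the ambiguous reading of *Possible* to express that.

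**Step 5. Trace which outputs depend on the rating.**

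- Dependent: vaccine-related TEAEs, related Grade 3 or higher TEAEs and related TESAEs (section 10.3.4), and the adverse-reaction limbs of sections 5.1.4 and 7.7.
- Not dependent: all TEAEs, all Grade 3 or higher TEAEs and all TESAEs (section 10.3.4), the endpoints worded to cover events as well as reactions, and SAE and AESI incidence (section 4.3).

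**The case against.** The strongest reply is that the protocol has other routes for a new reaction. *Possible* can be read so that plausible timing is enough. *Unlikely* needs a possible other cause, so novelty alone does not meet it. Section 8.3 has every SAE reported within 24 hours whatever its relation, sends doubtful SAE causality to an expert meeting, and requires expedited reporting when either party cannot exclude a relation. The suspension text acts on a SUSAR and does not limit that to the investigator's rating under section 4.5.3. Several serious neurological and cardiac conditions are listed as AESIs in section 4.5.4 and counted regardless of causality. An unreachable *Definite* loses no event from the related counts, since *Likely* lies below it.

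All of this stands, and it rules out some stronger inferences. A reader might infer that every related category demands a match to known information; the and/or in *Possible* does not support that. A reader might infer that new reactions are simply filed as *Unlikely*; without another cause they fall into a gap instead. A reader might infer that the related counts and the SUSAR trigger are emptied; known reactions still count as related, and section 8.3 keeps a route open for serious events.

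The reply leaves two gaps. The section 8.3 safeguards apply to serious events, so a new non-serious reaction, including a Grade 3 one, has none. Nothing in the protocol says that the ratings behind the section 10.3.4 tables are revised after a section 8.3 decision.

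**Conclusion.** The point holds as a defect in stated wording. Section 4.5.3 treats novelty as evidence against relatedness, contradicts the idea of a related but unexpected reaction used in sections 5.1.4, 7.7 and 8.3, and contains a category that NVSI-06-09 cannot reach.

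The direction of the bias is towards fewer events rated related. Its size cannot be derived from the protocol. One might compute an upper bound for zero related events in 258 participants (one-sided 95%: 1 − 0.05^(1/258) = 1.15%), but the protocol plans no such bound and known reactions would still be counted, so the figure does not measure this problem.

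The conclusion assumes that investigators follow the scale as written. It also depends on which grades the tables call vaccine-related, which the statistical analysis plan may settle and which is not itself a finding. If only *Likely* and *Definite* count, a new reaction cannot enter the related tables. If *Possible* counts too, entry depends on the reading of and/or. The effect is greatest for non-serious events, is partly contained for serious ones, and is absent from the all-cause and AESI summaries.

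**What to change.** In section 4.5.3:

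1. Remove consistency with known vaccine information as a condition of *Possible*, *Likely* and *Definite*, and remove inconsistency with known reactions from *Unlikely*.
2. Rate causality on timing, plausibility and alternative causes, worded so that an event with no other explanation has a clear category.
3. Assess expectedness separately, at the sponsor's SUSAR step in section 8.3.
4. Remove the repeat-exposure condition from *Definite*, or drop that category.

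Then reconcile section 4.5.3 with the suspension criteria in sections 5.1.4 and 7.7 so that they use relatedness in the same sense. The content of those criteria is for the sponsor and investigators to decide.

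The cost is protocol text and eCRF guidance, with no extra visits or staff. Slightly more events may be rated related. The change is best made before causality is assessed, because ratings already given under the present wording would have to be reviewed again.

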**CONFIDENTIAL**

**Definite:** Adverse events are consistent with the known investigational vaccine information and have a causal relationship with the investigational vaccine, and this relationship cannot be explained by other factors, such as the clinical status of the participant, other treatments or accompanying drugs. In addition, adverse events occurred repeatedly when the participants used the investigational vaccine again.

#### **4.5.4 Adverse Event of Special Interest**

According to the CIOMS VII definition, AESI refers to a class of scientific and medical events (including serious or non-serious) related to investigational vaccines or projects, which require investigators to continuously monitor and quickly communicate with the Sponsor. These events need further study to understand their characteristics; Depending on the nature of the event, the Sponsor also needs to communicate quickly with other relevant parties (such as regulatory authorities). The follow-up period of AESI is 12 months after the full course of immunization. AESI related to this vaccine include:

- Nervous system diseases (generalized convulsions, Guillain-Barre syndrome, acute disseminated encephalomyelitis, aseptic meningitis, general convulsions, peripheral facial paralysis, and loss of smell/ taste)
- Immune system diseases (vaccine-related respiratory diseases increase, anaphylactic shock, and multisystem inflammatory syndrome in children)
- Respiratory diseases (acute respiratory distress syndrome)
- Cardiac system diseases (acute cardiovascular injury including myocarditis, pericarditis, arrhythmia, heart failure, myocardial infarction)
- Blood system damage (thrombocytopenia, coagulation dysfunction including coagulation diseases, thrombosis, thromboembolism, internal/external bleeding, and stroke)
- Kidney system diseases (acute kidney injury)
- Liver system diseases (acute liver injury)
- Skin system diseases (chilblain-like lesions, single organ skin vasculitis, erythema multiforme, and alopecia).

#### **4.6 Randomization and Blinding**

**CONFIDENTIAL**

#### **4.6.1 Randomization**

A stratified block randomization method will be employed in the study. Interactive Web Response System (IWRS) will be used in participant randomization and vaccine allocation.

The randomization statistician will produce a participant randomization list and vaccine randomization list by SAS 9.4 (or later version), which will be imported into IWRS by the system engineer. After one participant is screened successfully, the investigator at each centre will log onto IWRS to get the randomization number of the participant. Before vaccination, the investigator will receive the vaccine number from IWRS and inoculate vaccines accordingly. If the vaccine is damaged, the investigator could acquire a new vaccine number from IWRS and inoculate the vaccine with a new vaccine number.

#### **4.6.2 Blinding**

Before the start of the study, the staff from Sponsor who will not participate in the clinical trial will blind the vaccines to be used in the study together with the unblinded randomization statistician. The vaccine label will be stuck on the specified position of each vaccine according to the vaccine randomization list. The randomization statistician will supervise and guide the process of blinding. After blinding is completed, the vaccine randomization list will be sealed by the unblind randomization statistician. The whole blinding process will be recorded and written in a document named blinding records, which is one of the important documents of this trial. The blinding personnel cannot participate in other related works of the trial, and they are not allowed to disclose the blind code to any personnel who are participating in the trial.

The participant randomization list and vaccine randomization list will be sealed, including the blind code composed of parameters like the code corresponding group assignment, the seed number generating random codes, etc. The blind code will be well sealed and saved until the database is locked.

#### **4.6.3 Emergency Unblinding**

In an emergency, when the investigator thinks that the group assignment information of one participant is beneficial for the handling of adverse events, it will be broken through the

**CONFIDENTIAL**

Emergency Unblinding Module in IWRS. The investigators need to discuss with the Sponsor and both shall reach an agreement before performing emergency unblinding.

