**CONFIDENTIAL**

respectively, the participants were followed-up by telephone and guided to observe the adverse events correctly and fill in the diary card.

3. On the 14th day after vaccination, the investigator reviews the filling of the diary card during this period and re-collect the diary card.
4. On the 8th -28th day after vaccination, the investigator uses telephone follow-up once a week, combined with an active report of the participants to monitor the safety.
5. When it is known that the participant has adverse reactions/events of Grade 3 or above, a face-to-face visit should take place within 24 hours.
6. SAEs and AESIs are observed from the first dose to 12 months after the full course of vaccination via monthly telephone follow-up calls and self-reports from the participants.
7. Participants should contact the doctors on informed consent form/diary card immediately if developed any COVID-19 like symptoms.

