### 7.6 Concomitant Medication

Within 0-28 days, actively follow up and observe the local and systemic adverse events of the participants and record them on the vaccination diary card. At the same time, it is necessary to record the drug used of the participants on the vaccination diary card.

**Medication Allowed:** During the clinical trial, if the participant has adverse events, necessary medication and medical treatment should be allowed.

**Vaccines Allowed:** None COVID-19 vaccines are allowed during the trial, which should be carried out 15 days after the trial vaccination. Emergency vaccination, such as rabies vaccine and tetanus vaccine, is not restricted.

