## **8. SAFETY DEFINITION, REPORTING AND MONITORING**

### **8.1 General Precautions**

Before the start of the trial, the Sponsor shall strictly examine the trial site in accordance with GCP requirements, focusing on whether the environmental facilities of the trial site meet the requirements of "Vaccination Management Standards" and "Guiding Principles for Quality Management of Vaccine Clinical Trials". Ensure the first aid facilities and first aid equipment in the first aid room are complete and effective, and the first aid doctors have corresponding qualifications and capabilities. Emergency related personnel (emergency doctors, emergency nurses, ambulance drivers, etc.) are trained to be qualified and familiar with the transfer routes and procedures of the agreed hospital. They are on standby at the trial site during vaccination. The trial site shall be equipped with ambulances. The ambulance shall be parked in a fixed position to keep the vehicle in good condition and in an emergency and shall be under the command and transfer of the emergency response team at any time. During the vaccination period, the agreement hospital will make daily preparations for medical personnel, instruments and equipment, first aid drugs and first aid sites to ensure that the participants can receive timely treatment. The trial site shall formulate an emergency plan, stipulate personnel responsibilities, contact numbers, rescue routes and other measures to ensure timely handling of unexpected adverse events, and ensure effective contact between participants and investigators so that any adverse events can be reported and handled quickly.

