#### **(1) On-site Treatment Measures**

Emergency plans for SAE treatment in clinical trials shall be established at the trial site, and all relevant personnel shall be trained. If the participants show serious adverse events, the investigators shall immediately take appropriate measures for the participants and record them. The investigators must take relevant approaches to know in time any clinically significant diseases/events related to vaccination. According to relevant national regulations, the participants should be received appropriate treatment in time in the designated hospitals.

Investigators at the trial site should follow up serious adverse events until the symptoms disappear or stabilize. The progress and outcome of all symptoms will be recorded in detail, and all drug treatments and medical treatments will be recorded at each follow-up.

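### Section 4.6.3 makes the sponsor's prior agreement a condition of emergency unblinding, with no exception and no rule if the sponsor is unreachable or disagrees

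*Protocol*

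**What the plan says.** Section 4.6.3 starts from the investigator's judgement. The code may be broken in an emergency "when the investigator thinks that the group assignment information of one participant is beneficial for the handling of adverse events", using the emergency module of the IWRS. The section then ends with the condition "The investigators need to discuss with the Sponsor and both shall reach an agreement before performing emergency unblinding".

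Two neighbouring sections complete the picture. Under Section 4.6.1, "the investigator at each centre will log onto IWRS to get the randomization number of the participant", so sites work in the IWRS themselves. Under Section 4.6.2, "The blind code will be well sealed and saved until the database is locked", so Section 4.6.3 is the only route to an individual allocation before database lock.

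**The concern.** An emergency code break exists so that the clinician responsible for a participant can learn the allocation when it bears on care. Section 4.6.3 accepts that purpose and leaves the judgement to the investigator. It then makes acting on that judgement depend on a second party's consent. The consent has no time limit, no named sponsor role to give it and no fallback.

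An investigator who thinks the allocation would help, but cannot obtain agreement, has two options: wait, or depart from the protocol. What is at stake is participant safety in that narrow situation. The statistical results are not involved.

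**Working it through.** No arithmetic applies. The check was to read the rule closely and then look for any other text that might relax it.

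**1. The rule itself.** The wording is mandatory (both parties shall agree) and comes first in time (before unblinding is performed). Three situations can follow:

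| Sponsor's position | What Section 4.6.3 permits |
|---|---|
| Reached and agrees | Code break |
| Reached and disagrees | Nothing stated; the condition is not met |
| Not reached | Nothing stated; the condition is not met |

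In the last two rows the investigator has no permission to proceed, whatever the clinical judgement.

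**2. Possible exceptions elsewhere in the protocol.**

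- *Section 4.6.2, Blinding.* The code stays sealed and the blinding personnel may not disclose it. This offers no alternative route.
- *Synopsis (Trial Completion), Sections 7.10 and 9.* These deal with unblinding for analysis, not for an individual emergency.
- *Section 8.3 (1), On-site Treatment Measures.* For serious adverse events "the investigators shall immediately take appropriate measures for the participants and record them". This is a duty to treat; it says nothing about the code.
- *Section 8.3 (2), sponsor reporting.* There is a rule for disagreement between investigator and sponsor, but it covers causality and expedited reporting only.
- *Section 11.1.* There is an exception for imminent hazard, but it concerns putting a protocol amendment into effect before ethics approval.

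None of these relaxes the condition in Section 4.6.3.

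**3. What the rule does and does not hold back.**

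- *Treatment.* Section 7.6 says that "if the participant has adverse events, necessary medication and medical treatment should be allowed", and Section 8.3 (1) requires immediate action. Neither depends on the code.
- *Later dosing.* The Synopsis (Study Design) gives one booster dose, so no further study dose depends on the allocation.
- *Period.* Section 7.3.1 states that "SAEs and AESIs are observed from the first dose to 12 months after the full course of vaccination", so the need for a code break is not confined to the vaccination day.

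What remains is a decision on handling an adverse event that the investigator thinks the allocation would inform.

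**The case against.** The strongest case on the other side is that no consequence is shown. The protocol names no event whose treatment would differ by arm. Both arms receive one dose of an active vaccine, and treatment can begin without the code. The wording of Section 4.6.3 is that the allocation is beneficial, not that it is needed, and handling an adverse event is not defined as treating it. Emergency plans and safety procedures required by Sections 8.1, 8.3 and 8.3 (1) are not shown and might contain sponsor contact arrangements.

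Most of this stands, and it limits the weight of the point. It does not remove the point. The protocol fixes the rule expressly, and nothing in it says that another document overrides the rule.

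A reader might also infer more than the text supports:

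- *That urgent treatment is delayed.* Sections 7.6 and 8.3 (1) rule this out.
- *That an allocation needed for care is withheld.* The section speaks only of benefit. Need is a stricter standard that the protocol does not use.
- *That the IWRS blocks the investigator.* The protocol does not say that the module enforces sponsor approval. The restriction is one of permission, not a demonstrated system lock.
- *That protection lapses after vaccination day.* Section 8.1 does say of emergency staff that "They are on standby at the trial site during vaccination". But the treatment provisions in Sections 7.6 and 8.3 (1) are not limited to that day.

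**Conclusion.** The point holds in a limited form. Section 4.6.3 gives the sponsor a power to delay or veto an emergency code break that the investigator judges useful for care. No other text in the protocol qualifies that power. This is a stated rule that is badly fixed, not a detail left to another document.

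The size cannot be given as a number, because the protocol states no expected frequency of emergency code breaks. For the trial's results the effect is nil: the 516 participants, the immunogenicity comparisons and their error rates are unaffected.

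The conclusion rests on two assumptions: that sites follow Section 4.6.3 as written, and that no procedure outside the protocol already grants the investigator sole authority. The change is worth making because it is cheap and removes a conflict between following the protocol and acting on clinical judgement. It is not a defect that threatens the trial.

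**What to change.** Replace the last sentence of Section 4.6.3 with:

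> In an emergency the decision to unblind rests with the investigator, who may break the code for that participant through the IWRS Emergency Unblinding Module when the allocation is judged necessary for the participant's care. Discussion with the Sponsor beforehand is encouraged where time permits but is not a condition. The investigator notifies the Sponsor within 24 hours without disclosing the allocation and records the date, time and reason.

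Align the trigger in the section's opening sentence with this text so that a single standard applies. One rule for all emergencies avoids asking the investigator to sort them into urgent and non-urgent before acting, and it leaves no residual case in which agreement is still required. The 24 hours matches the limit in Section 8.3 (2) for the initial report of a serious adverse event, which is likewise a limit on giving notice.

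The cost is a few sentences of protocol wording and, rarely, a code break that prior discussion would have avoided. The stricter trigger (necessary for care, where the present text asks only for benefit) and the written record keep that cost small. Withholding the allocation from the notice keeps the sponsor blinded.
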